The non-invasive brain stimulation therapy will be transcranial direct current stimulation (tDCS) over the Primary Motor Cortex (M1). A tDCS over M1 is capable of increasing corticospinal excitability in both M1 and other pain processing-related areas such as thalamus, Dorsolateral Prefrontal Cortex (DLPFC), cingulate cortex and insula [15,16], also involved in PD pain processing [12]. These increments of cortical excitability have been correlated with pain relief in chronic pain such as fibromyalgia [19], osteoarthritis [20], migraine [21], and spinal cord injury [22]. It is also hypothesized that tDCS would be an effective strategy to treat central sensitivity-related pain [23], a process whose features are common with PD condition [3]. Moreover, specifically in PD, tDCS over M1 have shown to increase cortical excitability, augmenting the Motor Evoked Potential (MEP) amplitude by 78.5%, correlating with motor improvements [24]. The altered descending inhibitory systems in chronic pain could also be improved with high frequency repetitive transcranial magnetic stimulation, by increasing cortical excitability [25].

For the most part, the hypoalgesic effects generated by tDCS are due to the adjustment of its effect on the Primary Motor Cortex (M1). It is suggested that tDCS on M1 could reduce pain by increasing excitability, not only of the stimulated area, but also of other structures involved in pain processing, both sensory and emotional, such as the thalamus, dorsolateral prefrontal cortex (DLPFC), cingulate cortex, insula, and brain stem [15,16], thanks to cortical-subcortical connectivity [26].

Due to the coincidence between many of the most influential areas of pain in PD [12] and the areas excited by tDCS on M1, with these increases in excitability correlating with decreases in pain [15,16], there is a possible beneficial interaction between tDCS on M1 and pain in PD.

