#### 2.3.2. Secondary Outcomes

##### Psychological and Functional Outcomes

The emotional outcomes assessed will be depressive symptoms, measured by Beck Depression Inventory (BDI), anxiety, measured by Stait-Trait Anxiety Inventory (STAI) and fear of movement-related pain, measured by Tampa Scale of Kinesiophobia (TSK-11). Cognitive outcome assessed will be catastrophizing thinking, measured by Pain Catastrophizing Scale. Finally, the functional outcome assessed will be the Unified Parkinson’s Disease Rating Scale (UPDRS), the most used scale for the assessment of disability in PD patients.

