##### Neurophysiological Outcomes

The excitability of pain-related pathways will be measured by Transcranial Magnetic Stimulation (TMS) markers. Firstly, single pulse TMS will be performed to acquire resting motor threshold (rMT), motor evoked potentials (MEPs) and cortical silent period (CSP). Magstim Rapid2 device with a figure-of-eight magnetic stimulator coil will be used. For all assessments, the magnetic stimulator coil will be placed firstly on the right and secondly on the left M1 with a 5 min rest interval, and surface electromyogram from the contralateral first dorsal interosseous muscle will be recorded. TMS used amplitudes and EMG recordings will be recorded and stored in a computer for off-line analysis [66]. Stimulation output used to reach the rMT, MEP amplitudes and silent periods duration will be taken as outcomes.

Brain activity will be measured by Electroencephalography (EEG). An actiCHamp amplifier (Brain Vision LLC, Morrisville, NC, USA) will be used to amplify and digitize the EEG data at a sampling frequency of 512 Hz. The EEG data will be stored in a PC running Windows 7 (Microsoft Corporation, Washington, DC, USA). EEG activity will be recorded from 64 positions with active Ag/AgCl scalp electrodes (actiCAP electrodes, Brain Vision LLC, Morrisville, NC, USA). The ground and reference electrodes will be placed on AFz and on FCz, respectively Electroencephalography acquisition will be carried out by NeuroRT Studio software (Mensia Technologies SA, Paris, France). The EEG signal processing procedure will be performed using MATLAB functions (MathWorks Inc., Natick, MA, USA), specifically the EEGLab toolbox. The EEG registers performed will be resting (1 min), while FT task (30 s each hand, beginning with the dominant one), while wrist-extension task (5 min each hand, beginning with the dominant one) and with eyes closed (5 min). The participants will be asked to relax in the resting condition; the investigator will ensure they do not fall asleep, especially in resting and in eyes closed registers. Spectral entropy correlation, coherence and interhemispheric divergence differences among experimental group and controls will be analyzed as outcomes.

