### 2.4. Sample Size Calculation

#### 2.4.1. tDCS-Based Study

The simple size for the tDCS-based study was calculated using G*Power software (version 2.1, Heinrich-Heine-Universität Düsseldorf, Düsseldorf, Germany), taking into consideration the design of two intervention groups and three assessment times. The primary outcome was chosen to be King’s Parkinson’s Disease Pain Scale with an estimated effect size of F = 0.25. An α level of 0.05 and a power of 90% was assumed, with a total sample of 28 subjects estimated. Considering a 15% follow-up loss, we estimated a minimal sample size of 32 patients, with a minimal recruitment of 16 required for each of the intervention groups.

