### 2.5. Data Analyses

The SPSS software package (version 25.00; SPSS inc., Chicago, IL, USA) will be used by a blinded statistician for statistical analysis of the data. Demographic and clinical variables will be presented as mean and standard deviation. A 95% confidence interval (CI) will be taken, considering statistically significant all those values that had a *p* < 0.05. Parametric statistical tests will be used for hypothesis testing (*n* > 30). To show differences in the main variables, an analysis of variance (ANOVA) 2 × 3 of repeated measurements will be carried out taking time and group as factors, being the groups active-tDCS (a-tDCS) vs. sham-tDCS (s-tDCS) in the tDCS-based study and AO+MI-BCI vs. AO-control AO+MI-based study, and the measurements times pre-treatment, post-treatment, and at 15 days post-treatment. If significant differences are found in any of the interactions, a post hoc analysis will be performed with Bonferroni correction. The effect sizes will be calculated by means of the d of Cohen, being classified as small (d between 0.20 and 0.49), medium (d between 0.50 and 0.79), or large (d greater than 0.80) following the method of Cohen.

For the rest of the psychological variables, a Pearson’s correlation with the physical variables will be carried out in order to find relationships between both. Low correlation will be taken as that with values between 0.2 and 0.39; the correlation will be considered moderate when the value goes from 0.40 to 0.79; and high when the value of the correlation is greater than 0.80.

For the analysis of neurophysiological variables rMT, MEP magnitudes will be determined by averaging peak-to peak amplitudes. The ratio of the rMT, MEP amplitude recorded at each post-intervention time-point relative to the baseline rMT will be calculated [(MEP amplitude at each stage–baseline MEP amplitude)/baseline MEP amplitude Å~100]. Statistical analyses will be performed on the calculated test-to baseline MEP ratios. For the CSP values the time will be measured manually in each trial and averaged and the ratio compared to baseline measurement will be also calculated.

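### The MEP outcome is defined with two different baselines (rMT in the prose, MEP in the formula); on the likely reading it is a valid but skewed and generally less efficient percent change

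*Protocol article*

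**What the plan says.** The transcranial magnetic stimulation measures stand under "2.3.2. Secondary Outcomes". The Neurophysiological Outcomes subsection treats them as separate measures: "Stimulation output used to reach the rMT, MEP amplitudes and silent periods duration will be taken as outcomes". So rMT is a stimulator output, MEP is an electromyographic amplitude, and the cortical silent period (CSP) is a duration.

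Section 2.5 then defines the variable to be analysed in two consecutive sentences:

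- The prose: "The ratio of the rMT, MEP amplitude recorded at each post-intervention time-point relative to the baseline rMT will be calculated".
- The bracketed formula in the same sentence: change in MEP amplitude over its own baseline, with the denominator part reading "baseline MEP amplitude)/baseline MEP amplitude", expressed as a percentage. The garbled symbol before 100 is read as a multiplication sign and is not held against the plan.
- The next sentence: "Statistical analyses will be performed on the calculated test-to baseline MEP ratios".

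CSP is likewise to be expressed as a ratio to baseline. No formula is given for rMT. The same section states as a general rule that "Parametric statistical tests will be used for hypothesis testing", on the ground that n exceeds 30.

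**The concern.** The prose and the formula cannot both hold. Dividing an MEP amplitude by a baseline threshold gives a quantity with other units and another meaning than dividing it by the baseline MEP. As written, the denominator could be chosen after the data are seen, and a reader cannot tell how rMT itself will be analysed.

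Correcting the slip leaves a second issue. Percent change from baseline has a noisy measurement in its denominator: a doubling scores +100, a halving scores -50, and patients with small baseline amplitudes carry most weight. An arm can show a positive mean percent change when nothing has happened, which would invite comparison with the published result cited in the Introduction of tDCS "augmenting the Motor Evoked Potential (MEP) amplitude by 78.5" percent.

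Cortical excitability is the rationale for both treatments. Neurophysiological evaluation is the third part of the stated aim, and these variables also enter the regression on pain in Section 2.5. Even so, no primary conclusion rests on them.

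**Working it through.** **The definitions side by side.** Write B for baseline MEP, P for post-intervention MEP and T for baseline rMT.

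- Prose: P/T (and rMT/T for the threshold).
- Formula: 100 × (P − B)/B = 100 × (P/B − 1).
- Next sentence: P/B.

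The last two are linear transforms of each other and give identical t, F and p values. The conflict is therefore between two quantities: baseline rMT or baseline MEP in the denominator.

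**Plan figures.** The document states no N, power, SD or correlation for MEP, so there is no MEP figure to reproduce. The only sample-size statement concerns the King's pain scale: "An α level of 0.05 and a power of 90% was assumed, with a total sample of 28 subjects estimated". That gives 28/2 = 14 per arm, used below. The 78.5% rise in the Introduction is a background citation, used here only as an illustrative ratio of 1.785.

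**Within-arm mean when nothing changes.** Assume log-normal MEP with log-SD s at both visits and pre-post correlation ρ on the log scale. Then ln(P/B) has mean 0 and variance 2s²(1 − ρ), so the expected percent change is 100 × [exp(s²(1 − ρ)) − 1].

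- s = 0.3, ρ = 0.85: exp(0.0135) − 1 = about +1%
- s = 0.6, ρ = 0.7: exp(0.108) − 1 = +11.4%
- s = 0.6, ρ = 0.5: exp(0.18) − 1 = +19.7%
- s = 0.8, ρ = 0.7: exp(0.192) − 1 = +21.2%
- s = 0.8, ρ = 0.5: exp(0.32) − 1 = +37.7%

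**Between-arm comparison, by simulation.** A two-sample t test on percent change was compared with ANCOVA of log post-value on group and log baseline, two-sided 5%, 3,000 to 20,000 runs per setting.

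With no true effect, the percent-change test rejected in 0.041 to 0.052 of runs, so it is valid to slightly conservative. Percent change was right-skewed in every setting examined (population skewness about 0.5 to 4.4).

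Power at 14 per arm and a true ratio of 1.785:

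| log-SD | ρ | percent change | log ANCOVA |
|---|---|---|---|
| 0.3 | 0.5 | 0.998 | 1.000 |
| 0.6 | 0.5 | 0.61 | 0.79 |
| 0.6 | 0.7 | 0.84 | 0.91 |
| 0.6 | 0.85 | 0.993 | 0.994 |
| 0.8 | 0.5 | 0.35 | 0.55 |
| 0.8 | 0.7 | 0.58 | 0.71 |
| 0.8 | 0.85 | 0.89 | 0.93 |

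The loss here runs from about 0 to 20 points. At ρ = 0.3 and a coefficient of variation of 0.8 (log-SD √ln(1 + 0.8²) = 0.70), power was 0.319 against 0.577 at 14 per arm (26 points) and 0.371 against 0.641 at 16 per arm (27 points).

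For a smaller true increase of 40% at 14 per arm, power was 0.14 against 0.24 (coefficient of variation 0.8, ρ 0.3), 0.41 against 0.54 (0.5, 0.5) and 0.96 against 0.98 (0.3, 0.7).

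**Where the gain comes from.** At s = 0.6, ρ = 0.5, power was 0.61 for percent change, 0.68 for the log ratio without covariate and 0.79 for log ANCOVA. About 7 of the 18 points come from the log scale and 11 from adjusting for baseline.

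**The case against.** The strongest reply is that this is a one-word slip. The explicit formula and the sentence naming the tested variable both use baseline MEP, and only the prose mentions baseline rMT. That is fair and is the likely reading. It does not remove the need to correct the sentence, and it does not supply the missing definition for rMT.

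Several stronger conclusions are tempting but not supported:

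- A reader might infer that three different quantities are defined. Percent change and the ratio to baseline MEP give the same test, so there are two.
- A reader might infer that the contradictory denominators cause the skew. They do not. Skew and lost efficiency come from the percent-change metric; the contradiction leaves the definition open.
- A reader might infer that the trial could declare an effect where none exists. The spurious rise is a within-arm artefact. With no effect it is expected equally in both randomised arms and cancels in the active-versus-control comparison, which is the main hypothesis.
- A reader might call the MEP tests low-powered. Without an MEP SD, correlation or target effect in the document, that cannot be said: at a ratio of 1.785, power on percent change ranged from about a third to nearly 1 over the assumed inputs.

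Two further limits stand. The simulation uses one post visit and a simple two-arm test, whereas the plan has two post assessments, measures both hemispheres and names no specific test for MEP. And percent change is not always the worse choice against baseline adjustment on the raw scale: at coefficient of variation 0.8, ρ 0.85 and 14 per arm, its power was 0.95 against 0.89. The advantage claimed here is for adjustment on the log scale.

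**Conclusion.** The concern holds in a limited form. Section 2.5 contradicts itself on the denominator and gives no formula for rMT; this can be read off the page and needs no assumption. If the formula governs, the between-arm analysis is valid, but the outcome is right-skewed and its within-arm mean is biased upwards (about +1% to +38% for log-SD 0.3 to 0.8 and correlation 0.5 to 0.85). It was never more powerful than log-scale ANCOVA in any setting examined. The size of the loss, from nothing to 20 points over that range and somewhat more at lower correlation, rests wholly on a log-normal model with assumed SDs and correlations and on a borrowed ratio of 1.785. The outcome is secondary and the sample size does not depend on it, so severity is minor.

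**What to change.** In Section 2.5:

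- Delete the reference to baseline rMT as denominator, and delete the percent-change formula.
- Analyse log MEP amplitude and log CSP duration at the post-intervention visits by ANCOVA or a mixed model, with the log baseline of the same measure as covariate. Back-transform the group difference and report it as a between-arm ratio with its confidence interval.
- Analyse rMT separately, in stimulator-output units, with baseline rMT as covariate.

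The baseline values are already collected, so this changes analysis wording only: no extra visits, measurements or patients. The downside is that results appear as ratios rather than the percent changes some readers expect.

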## 1. Introduction

Parkinson’s Disease (PD) affects between 4.1 and 4.6 million people in the world [1]. The diagnosis of PD is currently clinical and based on its motor manifestations (bradykinesia, rest tremor and rigidity). However, non-motor symptoms such as pain, fatigue, and neuropsychiatric manifestations are present in more than 70% of subjects [2].

Pain affects about 85% of patients [3] but is paradoxically under-reported [4] and consequently under-treated in PD patients with a great impact in their quality of life [5]. Levodopa, which is the election treatment in PD, has shown controversial results regarding pain sensitivity [6,7] and has been shown to be ineffective for enhancing the endogenous pain modulation system [8]. Furthermore, there is a lack of management protocols and nonpharmacologic treatments for pain in PD [9].

Several syndromes are hypothesized to be involved in PD pain generation [10]. Generally, PD patients suffer from alterations in peripheral transmission, sensitive-discriminative processing, pain perception and pain interpretation in multiple levels, due to neurodegenerative changes in dopaminergic pathways, and non-dopaminergic pain-related structures [11]. Therefore, central mechanisms are proposed to be crucial for the development and establishment of pain in PD patients [12].

Regarding to pain processing features, PD patients have reduced pain thresholds [7], an augmented Temporal Summation (TS) after repetitive nociceptive stimulus [13] and the impairment of their Conditioned Pain Modulation (CPM) is correlated with a greater severity and premature onset of the disease [8].

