### 2.1. Study Design and Participants

The participants will be recruited in PD outpatient’s clinic of the Beata María Ana Hospital of Madrid, Spain. The subjects included will be assessed by a neurologist expert in movement disorders. All patients will be idiopathic PD patients diagnosed according to the UK Parkinson’s Disease Society Brain Bank criteria who suffer from whatever PD-related pain, determined by The Parkinson’s Disease Pain Classification System (PDPCS) [33] and with a pain intensity of 3 out 10 points in the Visual Analogue Scale (VAS) while in ON state, that is, when levodopa is acting. The rest of specific inclusion criteria and the exclusion ones are listed in Table 1 and Table 2. During the protocol, changes in analgesic medication during in the previous week or PD treatment in the previous month will be forbidden and if necessary, will lead to exclusion of the patient. Informed consent for all included procedures (therapies and outcomes measurement), approved by the ethics committee, will be obtained from all subjects before their inclusion, and both studies will follow the principles outlined in the Declaration of Helsinki.

Sensitive data for all participants will be registered separately, anonymized, and guarded according to current data protection European laws. All data will be registered and double checked in a database designed specifically for the studies.

Recruitment in both protocols will be made so placebo and active groups will be matched by age and the recruitment will be stratified in groups of subjects younger than 60 years and older than 60, always ensuring that there is an equitable number of subjects in the two sections.

It is well known that there are gender differences in pain thresholds in healthy humans [34] and some evidence suggests that greater disease severity, female gender and higher doses of mediation are associated with greater pain intensity in PD [35]. For this reason, inclusion of at least one third of female subjects will be assured. Disease severity and total dopaminergic daily dose will be controlled in the final analysis of results.

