A multiple linear regression analysis will be performed to estimate the strength of the associations between the rMT, PPT, CPM, TS, psychological and functional variables, and pain. CPM, TS and neurophysiological variables will be used as predictors. The strength of the association will be examined using regression coefficients (B), *p* values and adjusted R2. Standardized beta coefficients will be reported for each predictor variable.

For the EEG entropy analysis non-parametric Kruskal–Wallis (KW) tests will be performed to compare the distributions, Mann–Withney U test to evaluate the difference between the median values for Pre-intervention/Controls, Post-intervention/Controls or Pre/Post intervention, and non-parametric Wilcoxon rank-sum test for Pre/Post intervention, with a significance level of 0.05 and the alternative hypothesis of unequal values. Thus, small *p*-values will suggest significant differences between populations.

The first part of the analysis will consist of comparing the differences between ON state versus OFF state in pain intensity, conditioned pain modulation, and temporal summation, and the second part will investigate the effects of the intervention on these same variables comparing the differences between ON state versus OFF state. For this analysis repetitive measures of ANOVA will be performed followed by post-hoc test with Bonferroni correction using the interaction of group factor x state factor and time factor.

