## 3. Discussion

Our studies are very relevant in the quest for an effective non-pharmacological management of pain in PD. This symptom has a high prevalence and impacts negatively in the quality of life of affected subjects. Moreover, nowadays this matter becomes even more relevant because lack of physical activity produced because of pandemic mobility restrictions could increase pain. 49.7% of Spanish PD patients report having suffered from pain every day during the COVID-19 pandemic [67].

We propose two treatment strategies whose action mechanisms are compatible with the hypothesized pain mechanisms implied in PD and have been effective in the management of pain in other chronic pain conditions. Furthermore, both approaches are proposed to be applied in combination with conventional treatments, mainly based on exercise and dopaminergic medication, in order to enhance their effectiveness through predisposing the cortex to be more easily excited. Finally, both treatments, after the configuration and explanation, can be applied at home, facilitating independence and self-management, and maximizing the time out of medical centers. Future studies may combine tDCS over M1 with AO+MI-BCI if the results of both studies are satisfactory.

Additionally, our protocols will potentially give us valuable information about pain mechanisms and enlighten new solutions for its management in PD patients. For this purpose, firstly, we propose an integral evaluation of pain, not only measuring clinical pain, but also assessing the functioning of the descending pain modulatory system, the nociceptive pathways excitability, and possible peripherical and central hyperalgesia, establishing correlations between them. Secondly, we also have the intention to figure out whether emotional, cognitive, functional, neuropsychological, or neurophysiological aspects can influence on pain and its central processing in PD patients.

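### Section 2.1 promises control for disease severity and dopaminergic dose, but no model in section 2.5 contains either, so the regression coefficient of CPM on pain can be confounded

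*Protocol article*

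**What the plan says.** Four places in the protocol article bear on this.

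- **Section 2.5, scope of the regression.** A multiple linear regression is to "estimate the strength of the associations between the rMT, PPT, CPM, TS, psychological and functional variables, and pain". The secondary-outcomes section gives UPDRS as the functional outcome.
- **Section 2.5, predictors.** The next sentence reads: "CPM, TS and neurophysiological variables will be used as predictors". UPDRS, PPT and the psychological variables are not in that list. Regression coefficients, p values, adjusted R2 and standardised betas are to be reported.
- **Section 1, link to CPM.** In PD, "the impairment of their Conditioned Pain Modulation (CPM) is correlated with a greater severity and premature onset of the disease".
- **Section 2.1, link to pain, and a commitment.** The section cites some evidence that "greater disease severity, female gender and higher doses of mediation are associated with greater pain intensity in PD". The same paragraph then undertakes that severity and the total daily dopaminergic dose will be controlled when the results are finally analysed. It names no model and no severity measure.

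**The concern.** The general commitment in section 2.1 and the specific model in section 2.5 do not match. A statistician who followed section 2.5 to the letter would fit the pain regression without severity or dose.

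The omission matters more here than in the group comparison. Treatment is randomised, so leaving severity out of the 2 × 3 ANOVA does not bias the group effect. CPM is not randomised. If severity is related to both CPM and pain, a model without severity gives CPM part of the association that belongs to severity.

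The regression serves the study's mechanistic aim. The Discussion wants to learn "whether emotional, cognitive, functional, neuropsychological, or neurophysiological aspects can influence on pain and its central processing in PD patients", and in the sentence before it sets out to correlate clinical pain with the descending modulatory system. A CPM coefficient that partly reflects how advanced the disease is would be a poor basis for that.

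**Working it through.** **Step 1: does any model carry the promised control?** The analyses in section 2.5, with the terms each one names:

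| Analysis | Terms named | Severity or dose? |
|---|---|---|
| 2 × 3 repeated-measures ANOVA | group, time | no |
| Pearson correlations | psychological with physical variables | no |
| MEP, rMT and CSP ratios | value relative to baseline | no |
| Pain regression | CPM, TS, neurophysiological measures | not in the predictor list; UPDRS only in the scope sentence |
| EEG entropy tests | non-parametric comparisons | no |
| ON/OFF ANOVA | group, state, time | no |

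The section 2.1 commitment therefore has no place in section 2.5 where it takes effect.

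**Step 2: what could the omission do?** The plan gives no figure for this regression, so there is nothing to reproduce. What follows is an illustration with assumed correlations.

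Inputs from the documents: 28 patients from the sample-size calculation, 32 after allowance for loss to follow-up (section 2.4), and significance at p < 0.05 (section 2.5). Assumed: the correlation of severity with CPM, *a*; the correlation of severity with pain, *b*; and no association of CPM with pain once severity is held fixed.

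On the standardised scale the CPM slope without severity is then *a × b* in absolute size. With the Fisher approximation, *z* = atanh(*ab*) × √(n − 3), the chance of p < 0.05 is 1 − Φ(1.96 − *z*) + Φ(−1.96 − *z*).

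| *a* | *b* | Spurious slope | P(p < 0.05), n = 28 | P(p < 0.05), n = 32 |
|---|---|---|---|---|
| 0.1 | 0.3 | 0.03 | 5% | 5% |
| 0.3 | 0.3 | 0.09 | 7% | 8% |
| 0.3 | 0.5 | 0.15 | 12% | 13% |
| 0.5 | 0.5 | 0.25 | 25% | 28% |

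The last row at n = 28: atanh(0.25) = 0.255, times √25 gives *z* = 1.28, and 1 − Φ(0.68) is about 0.25.

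**Step 3: check with more predictors.** The approximation treats CPM as the only predictor. Simulation (6,000 data sets per setting, least squares, CPM plus four unrelated predictors, *a* = *b*) gave 6.7% at 0.3, 10.7% at 0.4 and 20.9% at 0.5 with n = 28. With n = 32 it gave 7.1%, 13.0% and 25.2%. With severity in the model, the rate at n = 28 was 5.0% to 5.3% in these settings. The four extra predictors are an assumption, since the plan gives no count.

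**Step 4: if CPM does have an association of its own.** Suppose its standardised slope given severity is 0.30. The slope without severity is 0.30 + (*b* − 0.30*a*) × *a*. For *a* = *b* = 0.3 this is 0.30 + 0.21 × 0.3 = 0.363. For *a* = *b* = 0.5 it is 0.30 + 0.35 × 0.5 = 0.475.

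**The case against.** The strongest reply is that section 2.1 already promises the control and excludes no model, and that the regression's scope sentence includes functional variables. On that reading the predictor list names only the variables of interest, and the adjustment set is a detail that a journal article may leave to a fuller document. Part of this stands: a reader might infer that the plan rules severity out altogether, and the text does not show that. It does not remove the point, because the mismatch lies between statements that the article itself makes.

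A reader might also infer that the CPM association is in fact confounded, or that severity is a common cause of impaired CPM and pain. The documents do not support that. They report associations, one of them hedged, and no coefficients. If severity raised pain only through impaired CPM, leaving severity out would not bias the CPM coefficient. Adjusting for it would not bias the coefficient in that case either, so the repair is safe under both accounts.

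Nor does the article promise a causal claim about CPM. The regression is described as estimating strength of association, and the Discussion sentence about influence on pain does not list CPM.

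Two practical cautions also stand. UPDRS is described as a disability scale, so its use as the severity measure needs the sponsor's confirmation. It is also measured after treatment, and the regression names no time point, so adjustment for a post-treatment value could bring in a bias of its own.

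**Conclusion.** The point holds as an inconsistency with a possible consequence. Section 2.1 commits to controlling for severity and dopaminergic dose, section 2.5 places them in no model, and the pain regression lists its predictors without them. Because the protocol relates severity to both CPM and pain, the CPM coefficient from the model as written can be confounded.

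The size is undetermined. Over the assumed correlations it runs from nothing of note to a false-positive rate about five times the nominal 5%. The figures assume that severity is the only confounder and is measured well. The case for including dose is weaker: it rests on the stated link between dose and pain and on the commitment itself, since the documents cite no link between dose and CPM.

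This is a minor point about a secondary analysis. The randomised comparison, the primary outcome and the sample size are unaffected.

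**What to change.** Reconcile the regression paragraph in section 2.5 with the commitment in section 2.1:

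- Enter baseline disease severity as an adjustment variable in the pain regression, using UPDRS or another severity measure that the sponsor confirms, together with baseline total dopaminergic daily dose.
- Make the scope sentence and the predictor sentence agree on which variables the model contains.
- Keep the predictor set small, given 28 to 32 patients per study.
- Report the CPM, TS and neurophysiological coefficients as adjusted associations, not as causal effects.
- State which other analyses the section 2.1 commitment covers.

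The cost is a few sentences and one or two degrees of freedom. UPDRS is already measured before treatment, and control for dose is already promised.

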### 2.3. Outcomes Measurement

The same outcomes will be included in both studies. All of them will be assessed by a trained physical therapist in all groups the previous week, the following week, and 15 days after the 10 intervention sessions. The procedure is presented in Figure 1.

Every outcome will be measured in the ON state of PD patients, 1 h after taking their dopaminergic medication, to ensure their comfort. Nevertheless, Kings Parkinson’s Disease Pain Scale (KPDPS), CPM and TS will be also measured in OFF state, 30 min before medication intake, to assess the effects of both neuromodulation therapies when dopaminergic medication is not acting.

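### Pre/post EEG entropy values from the same patients are assigned an independent-samples rank test, which is conservative and loses power when the two values are positively correlated

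*Protocol article*

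**What the plan says.** Section 2.5 (Data Analyses) of the protocol article sets out the EEG entropy tests in one sentence. After a Kruskal–Wallis test to compare distributions, it names the "Mann–Withney U test to evaluate the difference between the median values for Pre-intervention/Controls, Post-intervention/Controls or Pre/Post intervention", and then adds a further test: "and non-parametric Wilcoxon rank-sum test for Pre/Post intervention, with a significance level of 0.05". The tests are two-sided: "with a significance level of 0.05 and the alternative hypothesis of unequal values".

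Section 2.3 (Outcomes Measurement) gives the schedule for every outcome: "All of them will be assessed by a trained physical therapist in all groups the previous week, the following week, and 15 days after" the ten sessions. Each patient therefore contributes a pre and a post EEG value. No paired test is named for EEG.

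EEG is listed under section 2.3.2 (Secondary Outcomes), and the same outcomes apply to both trials.

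**The concern.** The Mann–Whitney U test and the Wilcoxon rank-sum test are algebraically the same procedure. Its null distribution assumes that the two sets of values are independent. Pre and post recordings from one patient are not. When they are positively correlated, which is the usual case for a stable within-person measure, the rank-sum statistic varies less than the test assumes. The p-values are then too large, the true error rate sits below the stated 5%, and the information in the pairing is thrown away. The paired rank test with the similar name is the signed-rank test.

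At stake is whether a real pre/post EEG change is detected. With at most 16 patients in an arm there is little power to spare.

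**Working it through.** **Inputs**

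- Test: Mann–Whitney/rank-sum, two-sided, 0.05 (section 2.5).
- Pairing: same patients before and after treatment (section 2.3).
- Patients per arm: 16 (section 2.4.1, "with a minimal recruitment of 16 required for each of the intervention groups"; section 2.4.2 adopts the same size).
- Pre/post correlation ρ and size of the EEG shift: **not in the article**. I assume ρ from 0.3 to 0.8, and shifts of 0.5 and 0.8 SD of a single measurement.

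The article gives no power figure for EEG to reproduce. Its sample size rests on the King's pain scale, "with an estimated effect size of F = 0.25", and does not bear on this point.

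**Step 1. True size, large-sample formula.** For bivariate normal pairs the rank correlation is (6/π)·asin(ρ/2), and pairing shrinks the variance of the rank-sum statistic by one minus that amount:

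true size = 2·[1 − Φ(1.96 / √(1 − (6/π)·asin(ρ/2)))]

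At ρ = 0.5: (6/π)·asin(0.25) = 0.483; √(1 − 0.483) = 0.719; 1.96/0.719 = 2.72; true size = 0.0064. The same formula gives 0.0202 at ρ = 0.3 and 0.0005 at ρ = 0.7.

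**Step 2. Size and power at 16 pairs, by simulation.** Bivariate normal pairs, two-sided 0.05. Ranges cover repeat runs.

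| ρ | True size, rank-sum | Power at 0.5 SD: rank-sum | Power at 0.5 SD: signed-rank |
|---|---|---|---|
| 0.3 | about 2% | 22% | 31–34% |
| 0.5 | 0.7–0.9% | 19–20% | 44–45% |
| 0.7 | 0.1% | 16–17% | 65–66% |

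The signed-rank test holds about 5% throughout. At ρ = 0 the rank-sum size is 4.7%, so the shortfall comes from the pairing. At 0.8 SD, rank-sum against signed-rank gives 57% vs 69% (ρ 0.3), 59% vs 84% (0.5) and 61% vs 97% (0.7).

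**Step 3. How much power is lost.** Fix the shift at which the signed-rank test has 80% power with 16 pairs:

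| ρ | Rank-sum power | Relative loss |
|---|---|---|
| 0.3 | 69% | 14% |
| 0.5 | 54% | 33% |
| 0.6 | 43% | 47% |
| 0.65 | 35% | 57% |
| 0.7 | 29% | 65% |
| 0.8 | 12% | 85% |

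The relative loss is nearly the same with 14, 28 or 32 pairs. It is larger for smaller shifts: at 0.5 SD and ρ = 0.5 it is 1 − 19/45 = 58%.

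**Step 4. The comparisons with controls.** Pre/Controls and Post/Controls set different patients against each other, so an independent-samples test is admissible there. On efficiency, the variance of a change score is 2(1 − ρ) times that of a post value: 1.4 at ρ = 0.3, 1.0 at 0.5 and 0.6 at 0.7. Testing change is therefore not automatically better than testing the post value.

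**The case against.** The strongest defence is that rank-sum is a slip for signed-rank. That is plausible, since naming one test twice serves no purpose. But Mann–Whitney is also listed for pre/post, so the slip would leave two conflicting tests for one contrast, one of them unsuitable. The text needs correcting on either reading. Nor is this a detail left to a fuller plan: the article names the tests, the level and the sidedness.

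It is also fair to say that EEG is secondary, that the main variables get a group-by-time repeated-measures ANOVA, and that the error leans toward caution. All of that stands and limits the weight of the point.

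A reader might infer more than the article supports:

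- *False positives rise.* They fall under positive correlation. Inflation would need a negative one (ρ = −0.3 gives 7.7%).
- *Most of the power is lost, or a real effect would probably be missed.* At a shift the paired test detects with 80% power, more than half is lost only from ρ of about 0.65 upward. At 0.8 SD the rank-sum test still has 57–61% power for ρ of 0.3 to 0.7. At 0.5 SD and ρ = 0.5 the signed-rank test itself has only about 45%.
- *The treatment effect is never tested.* Both trials are randomised, so Post/Controls at the same visit is a valid comparison of arms. It simply does not use baseline.
- *Kruskal–Wallis pools pre, post and control values.* Section 2.5 does not name its groups.
- *The outcome definition is also at fault.* The Neurophysiological Outcomes section states the contrast as "Spectral entropy correlation, coherence and interhemispheric divergence differences among experimental group and controls will be analyzed as outcomes". That is a between-arm contrast and contains no error.

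**Conclusion.** The point holds in a limited form. An independent-samples rank test, under two names, is prescribed for paired pre/post EEG entropy values, so the stated 0.05 is not the real error rate. With 16 patients in an arm the true size is about 2%, 0.7–0.9% and 0.1% at correlations of 0.3, 0.5 and 0.7. Against the signed-rank test at 80% power, the relative loss runs from 14% (ρ 0.3) to 85% (ρ 0.8).

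That the test does not match the data follows from the text alone. The size of the loss rests on assumed correlations, assumed shifts and bivariate normal values. The consequence is confined to a secondary outcome in each trial. It should be corrected before analysis, but it is not among the changes on which the trials' main conclusions depend.

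**What to change.** - **Pre/post within an arm:** replace both the Mann–Whitney and the rank-sum test with the Wilcoxon signed-rank test. If all three visits are compared within an arm, use the Friedman test.
- **Treatment effect:** compare the arms at the same post-treatment visit, preferably adjusting for the baseline EEG value already collected, for example by rank ANCOVA. A same-visit Post/Controls Mann–Whitney test may stay as a valid unadjusted comparison.
- **Kruskal–Wallis:** if it is kept, restrict it to independent groups.

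The cost is a few words in section 2.5. No new data, patients or visits are needed.
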